#### Exclusion Criteria

Patients meeting the following criteria will be excluded from the study: (1) those with comorbid or preexisting manic, hypomanic, or psychotic episodes; personality disorders or posttraumatic stress disorder; or alcohol or substance use disorders; (2) those with active suicidal ideation; (3) those who have not responded to CBT in the past; (4) those who have difficulty using VR devices and applications; and (5) those deemed inappropriate for this study by the principal investigator.

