### Sample Size Determination

The sample size will be 12 patients. This sample size was not determined on the basis of the distribution of any end point or statistical power.

In order to evaluate the acceptability of CBT-VR in this study, it is necessary to obtain data on use and satisfaction from a wide range of patients (based on parameters such as sex, age, and severity). In addition, a certain number of patients is necessary to evaluate efficacy and safety. A similar pre- and postintervention comparative study of CBT using VR for patients with depression (UMIN000040864) was conducted with 12 patients, and the number of patients was deemed to be sufficient for feasibility evaluation.

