#### Population for Efficacy and Safety Analysis

The population for efficacy analysis includes all participants who have used CBT-VR at least once and at least 1 end point is measured. The population for safety analysis consists of all participants who have viewed CBT-VR at least once.

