#### Analyses

Baseline characteristics will be assessed using descriptive statistics.

As a primary analysis, original scores and changes in the score on the HAMD-17 from baseline to the end of 16 sessions will be summarized, the latter depicted as mean and 95% CI values. A 1-sample *t* test against the null hypothesis that the mean change in score equals 0 will be performed. The threshold for statistical significance will be set at 5%, and multiplicity will not be adjusted since this study is exploratory by nature. Missing data will be imputed using the previous measurement.

As secondary analyses, original scores and changes in the scores on the HAMD-17 from baseline to other time points will be summarized, and mean and 95% CI values will be estimated. The same analyses will be performed for changes in MADRS, QIDS-SR, EQ-5D-5L, and CGI scores. The frequency and proportion of the patients in remission at each measured point and those with a decreased number or dose of psychotropic medications will be summarized. The frequencies and proportions of the patients who completed the 16 sessions, patient satisfaction, and usability (the Japanese version of Client Satisfaction Questionnaire-8 and other answers to questions) will be summarized for feasibility assessment. The time required for psychiatric consultation and the number of homework assignments done will be tabulated and summarized for each session. In addition, missing data will be excluded from the analysis at each measured point.

Detailed definitions for classification will be determined on the basis of the distribution before data fixation. The stratification variables for subgroup analyses are as follows: sex, duration of the current episode (<2 years and ≥2 years), age, work experience, previous CBT treatment, baseline HAMD-17 score, concomitant medications, homework compliance, time spent at the doctor’s office, continued viewing of VR content and use of applications (during follow-up).

As a safety analysis, the frequency of adverse events and failures will be tabulated for each event.

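### Patients with no measurement leave the remission denominator, while the primary HAMD-17 analysis at session 16 carries their last value forward

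*Protocol article*

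**What the plan says.** The Analyses section sets two rules for missing data. For the primary analysis, HAMD-17 change from baseline to the end of 16 sessions, it says: "Missing data will be imputed using the previous measurement". The paragraph on secondary analyses ends with: "In addition, missing data will be excluded from the analysis at each measured point". That paragraph covers "The frequency and proportion of the patients in remission at each measured point", along with satisfaction, usability, completion, consultation time and the count of homework assignments done at each session.

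Analysis sets are defined under Population for Efficacy and Safety Analysis. For efficacy, the definition reads: "The population for efficacy analysis includes all participants who have used CBT-VR at least once and at least 1 end point is measured". A similar definition is given for safety: "The population for safety analysis consists of all participants who have viewed CBT-VR at least once". Neither set is assigned to the feasibility end points.

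End Points and Evaluation Methods defines remission by thresholds on HAMD-17 and MADRS, response by a reduction of at least half on those scales, and the continuation rate as the share of participants who completed all 16 sessions. Study Outline has patients tested at treatment discontinuation and then followed up unless they leave the study.

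**The concern.** The trial asks whether CBT-VR is feasible and acceptable, and a favourable answer may lead to a confirmatory study. Patients who disengage are part of that answer. Under the secondary rule, a patient with no score at a time point is neither a remitter nor a non-remitter; the patient is simply not counted. If such patients tend to do worse, the remission proportion rises as they are lost.

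The mismatch with the primary analysis adds to this. Remission uses HAMD-17, the scale of the primary end point. A patient measured at baseline and session 8 but not at session 16 contributes a carried-forward change to the primary mean and nothing to session-16 remission. The two headline results would then rest on different patients.

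Per-session homework has a related problem. A patient who stops at session 5 has no homework record for sessions 6 to 16, and neither a discontinuation test nor later follow-up can supply one. Later-session summaries then describe only those still attending.

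**Working it through.** **Inputs.** Sample Size Determination gives N: "The sample size will be 12 patients". It adds: "This sample size was not determined on the basis of the distribution of any end point or statistical power". There is thus no planned rate, precision or dropout figure to reproduce. The number missing (m, 0 to 4) and the number of observed remitters (r, 4 or 6) are assumptions chosen to show a range.

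**Formulas.**
- As written (observed only): r / (12 − m)
- All enrolled, missing counted as not remitted: r / 12
- Difference: r·m / [12 × (12 − m)]

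| Missing m | 4 / (12 − m) | Points above 4/12 = 33.3% | 6 / (12 − m) | Points above 6/12 = 50.0% |
|---|---|---|---|---|
| 0 | 33.3% | 0 | 50.0% | 0 |
| 1 | 36.4% | 3.0 | 54.5% | 4.5 |
| 2 | 40.0% | 6.7 | 60.0% | 10.0 |
| 3 | 44.4% | 11.1 | 66.7% | 16.7 |
| 4 | 50.0% | 16.7 | 75.0% | 25.0 |

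**Precision.** With r = 4 and m = 3, the exact (Clopper-Pearson) 95% intervals are 13.7% to 78.8% for 4/9 and 9.9% to 65.1% for 4/12. The shift is small beside the sampling uncertainty of 12 patients, but if the missing do worse it runs in the device's favour.

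**Direction.** Take r = 4 and m = 3 again. The true proportion among the 12 lies between 4/12 = 33.3% (no missing patient remitted) and (4 + 3)/12 = 58.3% (all did). The observed-only figure of 44.4% is correct only if the missing remit at the observed rate, 3 × 4/9 = 1.33 patients. With 0 or 1 remitters among the missing, the truth is 33.3% or 5/12 = 41.7%, and 44.4% is too high. With 2 it is 6/12 = 50.0%, and 44.4% is too low. Inflation therefore depends on the missing doing worse.

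**Completion.** A patient who starts and stops has a known status, not completed, so the missing-data rule does not remove that patient. If dropouts did leave this denominator, the rate would be 100% by construction, which the end-point definition does not allow. Only a patient who never starts, or has no end point measured, could be lost, and only if the efficacy set were applied to completion. With 8 completers and 2 such patients (assumed), that would give 8/10 = 80.0% instead of 8/12 = 66.7%.

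**The case against.** Stopping treatment is not the same as missing data. Discontinuers are tested at discontinuation, the feasibility assessment includes a patient questionnaire, and the 3- and 6-month visits are timed from the intervention or from discontinuation. Many who stop can therefore supply remission and satisfaction data. This stands, and it lowers the likely number missing. It does not remove the problem: some patients will leave the study, and the Analyses section does not say whether a discontinuation test serves as the session-16 measurement.

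Homework is planned as a count with no stated percentage, and a patient who attends but does none contributes a zero. This also stands. The remaining issue is that a per-session count is hard to read without the number attending.

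The study is descriptive, no decision threshold depends on these rates, and frequencies are reported beside proportions, so with 12 patients a reader can see much of the missingness. That limits the harm but does not justify two different rules at one time point.

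A reader might go further and infer that acceptability is measured in a sample selected to accept the device, because the exclusion criteria remove "those who have difficulty using VR devices and applications". That criterion concerns eligibility and defines who the device is meant for. It has no bearing on the missing-data rule, and scoring people who never received CBT-VR as finding it unacceptable would mix eligibility with outcome.

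**Conclusion.** The point holds for remission, and for the satisfaction and per-session homework summaries where data are absent. As written, patients without a measurement leave these summaries, while the primary analysis retains them. For remission at N = 12, the gap from the all-enrolled rate is 3 to 17 percentage points with 4 remitters and 5 to 25 points with 6, for 1 to 4 missing. These figures rest on assumed numbers missing and on missing patients not remitting; with none missing the gap is zero.

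A reader might infer that completion is computed only among those who stayed, or that every feasibility proportion is biased towards the device. The documents support neither. Early stoppers are observed non-completers, no analysis set requires patients to have stayed, and the sets that require use of the device are written for efficacy and safety. Leaving the feasibility denominator unnamed in a condensed article calls for a clarification and is not itself an error.

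**What to change.** Amend the analysis wording as follows:

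- **Remission and response:** use all enrolled participants as the denominator at each time point, counting a missing assessment as non-remission and non-response. Give observed-only results as a sensitivity table, with the number missing at each point.
- **Completion:** state that the denominator is all enrolled participants, including any who never start.
- **Homework:** tabulate assignments done at each session beside the number attending out of all enrolled.

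No new patients, visits or assessments are needed. The cost is slightly less favourable reported rates. Counting missing as failure is deliberately conservative and gives the lower bound for remission, which is why the observed-only table should sit beside it.

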### Ethical Considerations

The clinical study will be conducted in compliance with the Clinical Trials Act. It was registered with the Japan Registry of Clinical Trials (trial ID jRCTs032220481) and approved by the Japan Certified Clinical Research Review Board. The study’s details will be fully explained to all patients, and face-to-face informed consent will be obtained before starting the study. After obtaining informed consent, the participants’ data will be deidentified before analysis.

If the obtained data are used in the future for purposes other than those indicated in this study, the following conditions will need to be met: (1) the study will be reviewed again and approved by the center's ethics committee or clinical research review committee, and (2) the willingness of the participants to cooperate in the study will be confirmed through reconsent or information disclosure regarding the conduct of another study.

## Results

This study was registered with the Japan Registry of Clinical Trials (trial ID jRCTs032220481). Informed consent will be obtained before enrollment in the study. Participant recruitment started on November 30, 2022, and data collection is ongoing as of September 2023. The results will be published in a peer-reviewed academic journal, presented at scientific conferences, and communicated to the participants and patient organizations. International Committee of Medical Journal Editors criteria on contributorship and authorship are applied.

## Discussion

This study is a first step toward testing the acceptability, feasibility, and preliminary efficacy and safety of introducing CBT-VR to patients with depression.

The efficacy of CBT for patients with depression who do not remit with pharmacotherapy has been verified in randomized controlled trials in Japan [3]. However, the provision of CBT to patients who wish to receive it is currently inadequate due to the large time burden on health care providers when conducting CBT and the lack of a system to provide CBT. In this study, we will evaluate whether it is possible to reduce the intervention time of health care providers while maintaining the therapeutic effects of CBT by replacing a portion of CBT conducted in person with VR and videoconferencing, using information terminals.

If this study confirms the feasibility of CBT-VR for depression, we may proceed to a confirmatory trial. Furthermore, if a future trial confirms that CBT-VR is effective, it may provide a new option for patients who have not had an adequate response to conventional treatment and have not had the opportunity to receive CBT.

As a limitation, the study will have a small number of cases, is not blinded, and will have no controls. In a future study, we would like to conduct a randomized controlled trial with appropriate controls.

Treatment options for CBT are expanding to include face-to-face, web-based, and VR components. Future developments may lead to new techniques, increasing access to CBT for more patients.

## Abbreviations

CBT: cognitive behavioral therapy
CBT-VR: virtual reality–based cognitive behavioral therapy
CGI: Clinical Global Impressions
DSM-5: Diagnostic and Statistical Manual of Mental Disorders, 5th Edition
HAMD-17: 17-item Hamilton Depression Rating Scale
MADRS: Montgomery-Åsberg Depression Rating Scale
QIDS-SR: Quick Inventory of Depressive Symptomatology Self-Report
UMIN: University Hospital Medical Information Network
VR: virtual reality
